## Abstract

**Background:**

Obesity is associated with a chronic systemic inflammatory process. Volatile or intravenous anesthetic agents may modulate immune function, and may do so differentially in obesity. However, no study has evaluated whether these potential immunomodulatory effects differ according to type of anesthesia in obese patients undergoing laparoscopic bariatric surgery.

**Methods/design:**

The OBESITA trial is a prospective, nonblinded, single-center, randomized, controlled clinical pilot trial. The trial will include 48 patients with a body mass index ≥ 35 kg/m^2^, scheduled for laparoscopic bariatric surgery using sleeve or a Roux-en-Y gastric bypass technique, who will be allocated 1:1 to undergo general inhalational anesthesia with sevoflurane or total intravenous anesthesia (TIVA) with propofol. The primary endpoint is the difference in plasma interleukin (IL)-6 levels when comparing the two anesthetic agents. Blood samples will be collected prior to anesthesia induction (baseline), immediately after anesthetic induction, and before endotracheal extubation. Levels of other proinflammatory and anti-inflammatory cytokines, neutrophil chemotaxis, macrophage differentiation, phagocytosis, and occurrence of intraoperative and postoperative complications will also be evaluated.

**Discussion:**

To our knowledge, this is the first randomized clinical trial designed to compare the effects of two different anesthetics on immunomodulation in obese patients undergoing laparoscopic bariatric surgery. Our hypothesis is that anesthesia with sevoflurane will result in a weaker proinflammatory response compared to anesthesia with propofol, with lower circulating levels of IL-6 and other proinflammatory mediators, and increased macrophage differentiation into the M2 phenotype in adipose tissue.

**Trial registration:**

Registro Brasileiro de Ensaios Clínicos, RBR-77kfj5. Registered on 25 July 2018.

**Electronic supplementary material:**

The online version of this article (10.1186/s13063-019-3399-z) contains supplementary material, which is available to authorized users.

## Background

Obesity, a major public health issue, has long been recognized as a precursor of morbidity and premature mortality [1]. An increasing number of morbidly obese persons - defined by the World Health Organization as having a body mass index (BMI) ≥ 40 kg/m^2^ [1] - are undergoing surgical procedures.

Obesity is a metabolic disorder associated with chronic systemic inflammation, predominantly originating from visceral adipose tissue (VAT). Adipose tissue is composed of a number of immune cells [2, 3]; among these, macrophages have been shown to be the predominant cell population [4]. In obesity, adipocyte expansion increases the secretion of monocyte chemoattractants that recruit inflammatory monocytes expressing type 2+ chemokine receptor (CCR2+) to the adipose tissue, where they differentiate into activated macrophages with the M1 phenotype [2]. M1 macrophages increase the production of proinflammatory cytokines such as tumor necrosis factor (TNF)-α, interleukin (IL)-6, and IL-12, and the generation of reactive oxygen species, such as nitric oxide (NO), via the iNOS pathway (NOS2) [2, 3].

Caution is required when choosing anesthetic agents for administration in morbidly obese patients, since these drugs may influence immune function and the inflammatory process [5]. In this context, anesthetics may interact with the perioperative inflammatory response, affecting the release of cytokines [6], the expression of cytokine receptors [7], phagocytic or cytotoxic action [8], and the transcription or translation of protein mediators [9, 10], resulting in potential beneficial or deleterious effects. Sevoflurane, a volatile anesthetic, exerts a number of effects on innate immunity, mainly inhibiting neutrophil function, decreasing lymphocyte proliferation, suppressing the release of cytokines from peripheral blood mononuclear cells and circulating monocytes, and affecting the function of natural killer (NK) and dendritic cells [8, 11, 12]. Propofol, an intravenous agent, has been shown to inhibit neutrophil chemotaxis [13], neutrophil oxidative response [14], macrophage phagocytosis [15], and bacterial clearance [16]. In a previous study, Heil et al. showed that in obese rats, anesthesia with propofol increased lung inflammation and airway resistance compared with dexmedetomidine and thiopental [17].

Previous studies compared sevoflurane with propofol on performance, effectiveness, recovery from anesthesia, and bispectral index (BIS) recordings (a marker of possible intraoperative awareness) [18, 19], but have not evaluated the immunomodulatory potential of these anesthetics in obese patients.

Overall, in centers with distinct expertise, the 30-day mortality rate in bariatric surgery is low (0.1–2%) [20], as is the rate of major complications (3.6% after gastric bypass and 2.2% after sleeve gastrectomy) [21]. However, apart from major and early complications, minor complications can still occur in the days following surgery, which may increase hospital length of stay. The inflammatory process is involved in the perioperative period, in which it impairs wound healing and increases the risk of infection. To date, no study has evaluated which anesthetic agent is associated with the least inflammation and fewest complications in obese patients undergoing surgery.

Therefore, we designed the OBESITA trial to assess the immunomodulatory effects of anesthetics and inform future sample size calculations for studies evaluating sevoflurane versus propofol in obese patients undergoing bariatric surgery. Our hypothesis is that anesthesia with sevoflurane will result in a weaker inflammatory response to surgery than anesthesia with propofol [17, 22].

## Methods

### Study design

The OBESITA study is a single-center, nonblinded, randomized controlled pilot trial with a 1:1 allocation ratio. A total of 48 patients scheduled to undergo laparoscopic bariatric surgery will be randomized to receive either inhalational anesthesia with sevoflurane or total intravenous anesthesia (TIVA) with propofol (see Consolidated Standards of Reporting Trials (CONSORT) diagram, Fig. 1) [23]. The protocol has been designed in accordance with the Standardized Protocol Items: Recommendations for Interventional Trials (SPIRIT) guidelines (Fig. 2) and the corresponding checklist (Additional file 1). Prior to surgery, patients will be approached by a member of the study team and informed written consent will be sought.

**Fig. 1 Fig1:**
[figure not shown]
Consolidated Standards of Reporting Trials (CONSORT) diagram. BMI, body mass index, KDOQI, Kidney Disease Outcomes Quality Initiative

**Fig. 2 Fig2:**
[figure not shown]
Standard Protocol Items: Recommendations for Interventional Trials (SPIRIT) diagram. Schedule of enrollment, interventions, and assessments for the OBESITA trial

### Inclusion criteria

Patients aged 18–59 years with BMI ≥ 35 kg/m^2^, scheduled to undergo laparoscopic bariatric surgery under general anesthesia, will be eligible. Preoperative management of patients in both groups will be consistent with current surgical best practice and at the discretion of the operating surgeon. Patients at risk of postoperative pulmonary complications (PPCs) will be identified using the Respiratory Risk Assessment in Surgical Patients in Catalonia (ARISCAT) score [24], which consists of seven independent predictors: three patient-related and four surgery-related predictors (Table 1). An ARISCAT score ≥ 26 denotes intermediate to high risk of PPCs. All medications used by patients will be queried during the preoperative interview with the anesthesiologist.

**Table 1 Tab1:** Independent predictors of risk for PPCs identified in the logistic regression model (ARISCAT score)

	Multivariate analysis OR (95% CI) *n* = 1.624*	β	Risk score^a^
Age, years			
≤ 50	1		
51–80	1.4 (0.6–3.3)	0.331	3
> 80	5.1 (1.9–13.3)	1.619	16
Preoperative SpO_2_, %			
≥ 96	1		
91–95	2.2 (1.2–4.2)	0.802	8
≤ 90	10.7 (4.1–28.1)	2.375	24
RTI in preceding month	5.5 (2.6–11.5)	1.698	17
Preoperative anemia (Hb ≤ 10 g/dL)	3.0 (1.4–6.5)	1.105	11
Surgical incision			
Peripheral	1		
Upper abdomen	4.4 (2.3–8.5)	1.480	15
Intrathoracic	11.4 (4.9–26.0)	2.431	24
Duration of surgery, hours			
≤ 2	1		
> 2–3	4.9 (2.4–10.1)	1.593	16
> 3	9.7 (4.7–19.9)	2.268	23
Emergency procedure	2.2 (1.0–4.5)	0.768	8

Three patients were excluded because of a missing value for some variables. Logistic regression model constructed with the development subsample, c-index = 0.90; Hosmer-Lemeshow chi-square test = 7.862; *P* = 0.447

*CI* confidence interval, *Hb* hemoglobin, *OR* odds ratio, *PPC* postoperative pulmonary complications, *RTI* respiratory tract infection, *SpO2* oxyhemoglobin saturation by pulse oximetry (breathing room air in the supine position)

^a^Simplified risk score was the sum of each logistic regression coefficient (β) multiplied by 10, after rounding off

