### Minimization of bias

Patients will be randomized using a computer-generated random number table, with an allocation ratio of 1:1. The allocation sequence will be implemented by a telephone call at the time of surgery. An investigator will collect data, and blood and adipose tissue samples will be coded so that the investigator evaluating the laboratory outcomes remains blinded to group allocation.

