### Samples

Blood (15 mL) will be collected in heparinized tubes prior to induction of anesthesia (baseline), immediately after anesthetic induction (T1), and before extubation (T2).

Two small fragments of subcutaneous adipose tissue and visceral adipose tissue will also be sampled. Each fragment will measure 2 × 2 × 2 cm after excess blood vessels and connective tissue have been removed with the aid of a scalpel, and will be obtained from surgical specimens that would be discarded immediately following gastroplasty.

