There are several patient-related (and thus nonmodifiable) factors associated with increased incidence of postoperative complications after bariatric surgery: male sex, preoperative BMI ≥ 60 kg/m^2^, open surgery, smoking within the last year, deep vein thrombosis, therapeutic anticoagulation, and serum albumin < 3.5 g/dL [91]. The duration and invasiveness of the surgical procedure may affect the inflammatory response, thus increasing the risk of bias [91], and will therefore be taken into account in this trial; these factors will be individually analyzed post hoc to isolate their interference with the outcomes of interest. The role of positive end-expiratory pressure (PEEP) in mechanical ventilation during general anesthesia for surgery remains uncertain. An ongoing randomized clinical trial is testing two different levels of PEEP: 4 cmH_2_O without recruitment maneuvers versus 12 cmH_2_O with recruitment maneuvers [35, 92]. In the present trial protocol, a PEEP of 5 cmH_2_O is suggested based on a secondary analysis of the international multicenter LAS VEGAS study, restricted to obese patients [93].

To our knowledge, only one prospective study has compared the effect of anesthesia with sevoflurane on inflammation to that of TIVA with propofol, in 54 adults undergoing thoracic surgery with one-lung ventilation [22]. The authors observed that the increase in inflammatory mediators such as TNF-α, IL-6, and monocyte chemoattractant protein 1 (MCP-1) was significantly blunted in the sevoflurane group. Sevoflurane was also associated with fewer postoperative adverse events [22]. A randomized controlled trial of 5400 patients, which compared volatile anesthetics to TIVA for elective cardiac surgery, showed that anesthesia with a volatile agent did not result in a significantly lower 1-year mortality rate compared to TIVA [94].

Moreover, in the experimental setting of obesity, a 1-h infusion of propofol resulted in increased airway resistance, atelectasis, and pulmonary inflammation mediated by increased TNF-α and IL-6 in lung tissue, with depletion of antioxidative enzymes [17]. Based on this evidence, we hypothesize that anesthesia with sevoflurane will result in a weaker inflammatory response compared to anesthesia with propofol.

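### The inclusion criterion is wider than the sleeve-or-bypass scope in the abstract, and type of operation, a plausible influence on IL-6, is left to post hoc analysis rather than balanced or adjusted for in advance

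*Protocol article*

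**What the plan says.** **Scope.** In the abstract (Methods/design), the 48 patients are those "scheduled for laparoscopic bariatric surgery using sleeve or a Roux-en-Y gastric bypass technique". The body of the article is wider. Under Study design: "A total of 48 patients scheduled to undergo laparoscopic bariatric surgery will be randomized". Under Inclusion criteria, adults in the stated age and BMI range "scheduled to undergo laparoscopic bariatric surgery under general anesthesia, will be eligible". Neither names a technique, and nothing under Exclusion criteria limits technique.

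**Allocation.** Under Minimization of bias: "Patients will be randomized using a computer-generated random number table, with an allocation ratio of 1:1". Allocation is obtained by telephone at the time of surgery. No strata or blocks are described.

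**Type of operation and inflammation.** The Discussion states: "The duration and invasiveness of the surgical procedure may affect the inflammatory response, thus increasing the risk of bias". The same sentence adds that this will be taken into account, and says how: "these factors will be individually analyzed post hoc to isolate their interference with the outcomes of interest". The Background gives different major complication rates for the two operations: "3.6% after gastric bypass and 2.2% after sleeve gastrectomy".

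**Analysis.** Under Statistical analysis, the arms are compared by Student's t test or the Wilcoxon test. No covariate is mentioned.

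**The concern.** There are two linked problems.

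First, the rule that decides who enters the trial is wider than the scope announced in the abstract. Read literally, it admits operations that the abstract does not cover.

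Second, the authors identify in advance a feature of the surgery that may drive the outcome, then leave it to be examined afterwards. Planned procedure is a baseline fact, available before the allocation call, so it can be balanced by design and adjusted for by a rule written beforehand. Duration of surgery is observed only after randomisation, so a post hoc analysis of it is a weaker tool: it may itself reflect events after allocation, and its form is chosen with the data in view.

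At stake is the precision of the IL-6 comparison, and how far a reader can trust it if the arms happen to differ in procedure mix. With 48 patients such a difference would not be unusual.

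**Working it through.** **1. The plan's own figure.** Inputs from Statistical analysis: effect size 1.33 (read as a standardised mean difference), two-sided α = 0.05, ratio 1. The two-sample t test with noncentral t distribution has noncentrality d√(n/2) and 2n − 2 degrees of freedom.
- n = 9 per group: power 0.755
- n = 10 per group: power 0.803, so the stated 10 per group for 80% is reproduced
- n = 24 per group: power 0.995

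Nothing in this point alters those figures.

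**2. Scope, side by side.**

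| Place | Eligible surgery |
|---|---|
| Abstract, Methods/design | sleeve or Roux-en-Y bypass |
| Study design | laparoscopic bariatric surgery, technique not named |
| Inclusion criteria | laparoscopic bariatric surgery, technique not named |
| Exclusion criteria | no limit on technique |

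**3. Chance imbalance without stratification.** The article gives no procedure mix, so the number of bypass patients, m, is an assumption. Take arms of exactly 24, as planned. The number X of bypass patients in one arm is hypergeometric:

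P(X = x) = C(m, x) · C(48 − m, 24 − x) / C(48, 24)

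For m = 24, the central value is P(12) = 0.227. In each tail, P(15) = 0.053, P(16) = 0.017, P(17) = 0.004 and P(18) = 0.001 (rounded). Then P(|X − 12| ≥ 3) ≈ 2 × (0.053 + 0.017 + 0.004 + 0.001), which is 0.148 before rounding.

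A difference of 6 patients is 6/24 = 25 percentage points between arms. The chance of at least that difference is:

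| Bypass patients (assumed) | Split | Probability of this or worse |
|---|---|---|
| 24 of 48 | 15 v 9 | 14.8% |
| 16 of 48 | 11 v 5 | 12.5% |
| 12 of 48 | 9 v 3 | 9.3% |

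With 24 of 48, the milder split of 14 v 10 or worse has probability 38.7%.

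**4. Effect on the arm difference.** If mean IL-6 differs by g between procedures, the unadjusted arm difference shifts by (difference in proportions) × g. For 15 v 9 this is (15/24 − 9/24) × g = 0.25g. The article gives no value for g. Assuming 0.5 to 1.0 within-procedure SD, the shift is 0.25 × 0.5 = 0.125 SD to 0.25 × 1.0 = 0.25 SD.

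**5. Effect on precision.** With a half-and-half mix, leaving procedure out of the model inflates the variance from 1 to 1 + g²/4: to 1.0625 at g = 0.5 and 1.25 at g = 1.0. Take a true effect of 0.827 SD, for which 24 per group gives 80% power when procedure is accounted for. Ignoring procedure lowers power to 78% at g = 0.5 and 71% at g = 1.0. At the plan's own effect size of 1.33 there is ample power and the loss is negligible.

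**The case against.** The strongest reply is that simple 1:1 randomisation is valid. Chance imbalance causes no systematic bias, and the error rate of the t test already allows for it. Under the half-and-half assumption, a split as bad as 15 v 9 is avoided about 85% of the time, and a shift of at most 0.25 SD is small beside a design effect of 1.33. Blocks and strata are also details that an article may leave to the full protocol, and this is a pilot that its authors call not conclusive. All of this stands and limits the point to efficiency and clarity. It does not remove it: the article states a post hoc approach to a factor that it names in advance, and that is a choice made, not a detail omitted.

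A reader might infer more, in four ways that the document does not support.

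- **That the plan ignores the type of surgery.** It does not. The Discussion commits to a post hoc analysis of duration and invasiveness, and Measurements records duration, pneumoperitoneum times and intra-abdominal pressure. The Discussion also does not name sleeve versus bypass; treating technique as a carrier of invasiveness is a reasonable inference, not a stated fact.
- **That adipose tissue comes only from sleeve patients, so those outcomes rest on a subset.** The Samples section says only that fragments are "obtained from surgical specimens that would be discarded immediately following gastroplasty". It does not distinguish operations. The inference needs surgical knowledge from outside the document, and the samples are subcutaneous and visceral fat, so whether stomach is resected does not settle whether they are available.
- **That other operations will in fact be enrolled.** The wording permits it, but this is a single centre and the article mentions only sleeve and bypass as techniques.
- **That the IL-6 comparison is biased.** An imbalance would be due to chance, not to the allocation method.

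**Conclusion.** The point holds in a limited form. The scope conflict between the abstract and the inclusion criterion is plain on the text; it is minor and easily resolved. The handling of procedure is a design weakness, not an error: the authors name a risk of bias and choose the weaker of the available remedies, although planned procedure could be balanced and adjusted for in advance.

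The size is modest: a 9% to 15% chance of an imbalance of at least 25 percentage points, and at 25 points a shift of 0.125 to 0.25 SD. This rests on three assumptions that the article cannot confirm: between a quarter and a half of patients having bypass, arms of exactly 24, and an IL-6 difference between procedures of 0.5 to 1.0 SD. If procedures do not differ in IL-6, the imbalance is harmless. The validity of the trial and its sample size calculation are not in question here.

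**What to change.** 1. **Scope.** Reconcile the Study design and Inclusion criteria with the abstract, so that the inclusion criterion names the procedures within the trial's stated scope. No further restriction is needed.
2. **Allocation.** Generate the list in randomly permuted blocks of varying size, stratified by planned procedure (sleeve / bypass). Have the planned procedure declared in the telephone call before the allocation is released.
3. **Analysis.** Prespecify planned procedure as a covariate in the IL-6 comparison, for example in a linear model on a suitable scale, or as the stratum in a stratified rank test if the Wilcoxon route is taken. Analyses of duration can remain, labelled exploratory.
4. **If the list can no longer be changed,** make the covariate adjustment alone, and fix it before any unblinded data are seen.

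The cost is one eligibility phrase, a two-stratum list and one more model term. The telephone procedure gains one question. The sample size is unchanged.

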### Exclusion criteria

The exclusion criteria are age < 18 years or > 59 years; insulin-dependent diabetes mellitus; anti-inflammatory and/or immunosuppressive therapies; a diagnosis of malignancy, chronic kidney disease (Kidney Disease Outcomes Quality Initiative (KDOQI) score > 3), liver disease (total serum bilirubin < 3 g/dL and total bilirubin > 5 mg/dL), or heart disease (New York Heart Association (NYHA) class III/IV); obesity caused by endocrine disorders; psychiatric illness that might interfere with capacity for formal consent and compliance; persistent smoking associated with significant obstructive lung disease (forced vital capacity (FVC) or forced expiratory volume in one second (FEV_1_) < 50% of predicted value) or restrictive lung disease (pre-bronchodilator FVC < 80% of predicted value and FEV_1_/FVC ≥ 0.7) [25]; alcohol dependence; pre-existing coagulation disorders; evident pulmonary or systemic infection (clinical diagnosis or any one of the following: C-reactive protein > 5 mg/L, leukocytosis with > 10,000 white blood cells (WBCs), or body temperature > 37 °C); autoimmune diseases; and participation in another randomized controlled trial within the preceding year.

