This study is the first step toward choosing an anesthetic strategy that is capable of reducing systemic inflammation in obese subjects (i.e., patients with chronic inflammation) undergoing laparoscopic bariatric surgery. Some studies have compared sevoflurane with propofol, but have focused on clinical consequences, such as intraoperative mean arterial pressure, eye opening, extubation, recovery from anesthesia, postoperative pain, and incidence and severity of postoperative nausea and vomiting (PONV) [18, 95], without understanding the mechanisms associated with clinical improvement.

Sevoflurane, a low-solubility inhaled anesthetic, is the first-line anesthetic agent of choice in Brazil. It has been shown to have a cardioprotective effect, preventing myocardial ischemia and arrhythmias [96], even though like other anesthetic agents it may cause hypotension [97]. A study determined that the minimal alveolar concentration (MAC) for sevoflurane needed to maintain the BIS at < 50 in morbidly obese patients undergoing bariatric surgery [98] was 1.8–1.6%, higher than those values previously reported in normal adult patients (0.97%; 95% CI 0.89–1.1%) and lower than those reported in children (2.8%; 95% CI 2.7–3.1%), which justifies the minimal MAC of 1.0 defined for this protocol. Moreover, a double-blind randomized controlled trial in superobese patients (BMI > 50 kg/m^2^), in which the performance, effectiveness, and recovery from anesthesia was compared for sevoflurane versus propofol in combination with remifentanil, showed that although both propofol and sevoflurane provided adequate general anesthesia, sevoflurane may be preferable in the superobese due to superior hemodynamic stability and faster recovery [18].

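### The liver-disease exclusion limits total bilirubin twice; one limit is always met, so the criterion cannot work as a two-part rule

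*Protocol article*

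**What the plan says.** In the protocol article, the section Exclusion criteria lists liver disease among the excluding diagnoses and defines it in brackets as "total serum bilirubin < 3 g/dL and total bilirubin > 5 mg/dL". Both limbs concern total bilirubin. The first is an upper limit in g/dL, the second a lower limit in mg/dL, and *and* joins them. No other part of the article restates or corrects the rule.

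Liver function returns under Study endpoints, Secondary. There, acute liver failure is one of the postoperative complications, defined by day-5 to day-1 ratios of bilirubin and INR, or by encephalopathy with a raised INR.

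**The concern.** A two-part exclusion should test two things. This one tests a single quantity twice, and one of the tests cannot fail. The g/dL unit and the less-than direction suggest that the first limb was meant for a different analyte. If so, whatever that limb was to screen for is not screened as designed, and staff applying the criterion literally would use a different rule from the intended one.

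At stake is the make-up of the enrolled sample with respect to liver function. Some patients may be admitted or turned away contrary to the sponsor's intention. The primary endpoint, plasma IL-6, is not directly involved.

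**Working it through.** **Inputs** (protocol article, Exclusion criteria): first limit, total bilirubin < 3 g/dL; second limit, total bilirubin > 5 mg/dL; connector, *and*. The article derives no figure from this rule, so there is none to reproduce. The sample-size calculation does not use it.

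**Step 1: common unit.** 1 g/dL = 1000 mg/dL, so 3 g/dL = 3 × 1000 = 3000 mg/dL. Relative to the companion limit this is 3000 / 5 = 600 times as high.

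**Step 2: the rule as printed.** Exclude if bilirubin < 3000 mg/dL and bilirubin > 5 mg/dL. On a grid of bilirubin values from 0 to 100 mg/dL, the first condition holds everywhere, and the rule gives the same answer at every point as bilirubin > 5 mg/dL alone.

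**Step 3: can a small repair rescue it?** Write b for bilirubin in mg/dL.

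| Reading | Condition for exclusion | Result |
|---|---|---|
| As printed | b < 3000 and b > 5 | Same as b > 5 |
| Unit of first limb changed to mg/dL | b < 3 and b > 5 | No one excluded |
| Connector changed to *or*, g/dL kept | b < 3000 or b > 5 | Everyone excluded |
| Both changed | b < 3 or b > 5 | Only values from 3 to 5 remain eligible, so low values are excluded as liver disease |

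No reading with bilirubin in both limbs gives a sensible two-part rule.

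**Step 4: direction of the consequence.** Let B be the patients with bilirubin > 5 mg/dL, and X the patients who meet the intended first limb, whatever it is. The printed rule excludes B.

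- If *and* was intended, the target set is X ∩ B, which lies inside B. The printed rule then excludes too many, namely those in B but not in X.
- If *or* was intended, the target set is X ∪ B, which contains B. The printed rule then excludes too few, namely those in X but not in B.

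The size of either group cannot be computed. The article names no other analyte for X and gives no distribution of liver tests in the target population.

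**The case against.** Four counter-arguments deserve an answer.

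**It could be an artefact of text extraction.** This is unlikely. The sentence is unbroken, no gap or redaction is marked, and the two limbs are worded slightly differently.

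**The rule still works.** It does, as a single limit of bilirubin above 5 mg/dL. This stands, and it is why the finding is a malformed criterion and not an absent one.

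**The harm may be small or run the other way.** This also stands. A reader might infer that patients with liver impairment are being enrolled and that safety and the liver endpoint suffer. Under the printed *and*, the always-true limb makes the exclusion broader than a true two-limb rule. Wrongly enrolled patients arise only if *or* was meant, and the article does not settle that. Acute liver failure is one item in a long list of secondary complications, and its bilirubin and INR part uses within-patient ratios. Alcohol dependence and pre-existing coagulation disorders are excluded separately.

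**The infection rule in the same section might look like a second error of this kind.** It excludes "evident pulmonary or systemic infection (clinical diagnosis or any one of the following: C-reactive protein > 5 mg/L", or leukocytosis or raised temperature, so CRP above 5 mg/L alone suffices. The Discussion describes the population as "reducing systemic inflammation in obese subjects (i.e., patients with chronic inflammation". A reader might conclude that the trial removes its most inflamed patients and answers its question in the least inflamed subset. The documents do not support that:

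- Eligibility rests on BMI and scheduled surgery ("Patients aged 18–59 years with BMI ≥ 35 kg/m^2^, scheduled to undergo laparoscopic bariatric surgery under general anesthesia, will be eligible"), not on inflammation.
- A sensitive infection screen is defensible in a small pilot with IL-6 as primary endpoint.
- The Discussion defends other exclusions on similar grounds, because those conditions add inflammation beyond that of otherwise healthy morbidly obese patients. It does not mention CRP there.
- No CRP distribution is given. If a share p exceeded the limit, 48 / (1 − p) otherwise eligible patients would have to be screened. Assumed shares of 20% and 80% give 60 and 240, a range too wide to conclude anything from.

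What remains is an awkward label, not an error.

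**Conclusion.** The liver-disease exclusion is wrong as written. One of its two limbs has no effect, and the printed rule equals bilirubin above 5 mg/dL. This follows from the text and a unit conversion and needs no outside assumption. That a different analyte was meant is an inference from the unit and the direction of the inequality; which one cannot be told from the article.

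The effect on enrolment is conditional: too few exclusions if *or* was intended, too many if *and* was intended. Its size is unknown. Eligibility is decided before randomisation and in the same way for both arms, so the between-arm comparison of IL-6 is not biased. What is affected is who is studied. The documents do not support a stronger claim about safety, the liver endpoint or the CRP limit.

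**What to change.** The sponsor should reconcile the criterion by stating (a) the intended analyte and unit of the first limb and (b) whether the limbs are joined by *and* or *or*. The analyte, the limits and the connector are for the sponsor's clinicians to settle; none is proposed here.

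The cost is a wording amendment to the eligibility section. The article implies no new measurement, but its text does not list the preoperative liver tests, so the sponsor should confirm that the intended analyte is already available. The correction may slightly change who is eligible in either direction. If patients have been screened under the printed wording, it should be recorded which version applied to them.

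Optionally, in the same amendment, the sponsor could state whether restricting enrolment to patients with low CRP is deliberate, since calling an isolated CRP above 5 mg/L evident infection sits awkwardly with the Discussion's description of the population.
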